## Statistical analyses

### Power Analysis

In order to assess the efficacy of the experimental intervention, a power analysis was performed. As reported by Sockol et al. (83), available psychosocial interventions for perinatal depression have been found to have an overall effect size of 0.65. Therefore, the sample size has been defined selecting 0.65 as desired level of effect size, an α error set at 0.05 and power set at 0.95. Therefore, the total sample will consist of 126 patients, allocated with a 1:1 ratio to the experimental or to the control group (Figure 1).

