### Data Analysis

Differences in socio-demographic and clinical characteristics, such as severity of depressive and anxiety symptoms, quality of life, trimester of pregnancy, and personal functioning between the two groups will be evaluated using Chi-square or *T*-test for independent samples, as appropriate. Differences in coping strategies and in family accommodation reported by relatives will be evaluated with the same tests.

In order to assess the efficacy of the experimental intervention, a linear multivariable regression model will be implemented, using as main outcome the score at HAM-D at 3 months post-randomization. Moreover, several confounding variables (such as age, marital status, familiarity for mental disorders, peer support, previous pregnancy, etc.) will be entered in the model. Furthermore, predictors of response at the end of the intervention will be identified.

“Response” is generally defined as a 50% decrease in scores on Hamilton Depression Rating Scale (HAMD) (74). In this protocol, we will consider the score at the 3-month HAM-D compared with the baseline score. Therefore, the continuous variable “3-month HAM-D score” will be transformed in a binary variable (1 = response; 0 = absence of response), and it will be entered in a logistic regression multivariate model in order to identify possible predictors of positive response to the experimental intervention.

In order to evaluate differences in relatives' coping strategies according to patients' clinical features and type of relationship with the patient, a two-level model with fixed independent variables and random intercept, using a maximum likelihood estimation, will be performed. The mean score at the subscales of the FCQ will be entered in the model, adding covariates step by step in order to identify the model with indexes of best fit. The final model will be selected according to the−2 loglikelihood value, and the model with the lowest value will be choose. Estimate, standard error, 95% confidence interval, and *P*-values will be calculated.

The level of significance will be set at *p* < 0.05. All analyses will be performed using the Statistical Package for Social Science software (SPSS), version 18.0 (SPSS).

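### The logistic response model, as described, cannot separate predictors of response to the experimental intervention from general prognosis

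*Protocol article*

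**What the plan says.** The Data Analysis section of the protocol article first describes the efficacy analysis, a linear multivariable regression of the 3-month HAM-D score with several confounders. It then adds: "Furthermore, predictors of response at the end of the intervention will be identified". Response means a 50% fall in HAM-D from baseline to 3 months, and the 3-month score "will be transformed in a binary variable (1 = response; 0 = absence of response". The purpose of the model built on this variable is stated more narrowly: "it will be entered in a logistic regression multivariate model in order to identify possible predictors of positive response to the experimental intervention".

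The section does not say whether one or both arms enter the logistic model, whether arm is a term in it, or whether any interaction with arm is fitted. No other section mentions an interaction, moderator or subgroup analysis of response.

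Three other sections matter here:

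- **Primary Outcome:** the working hypothesis compares BTO plus the intervention with BTO alone, so women in the experimental arm also receive BTO.
- **Inclusion Criteria:** women may enter at any time from beyond 3 months of gestation to within 3 days of childbirth.
- **Discussion:** childbirth itself may lower depressive symptoms, and family support, changed routine and starting medication may also affect outcome.

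**The concern.** The aim is about response to one particular treatment, so it is a question of effect modification: for which women is the difference between arms larger? A model of who responds answers a different question, namely which women do well.

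The two can diverge sharply in this trial. By the protocol's own account, HAM-D at 3 months can move for reasons unrelated to the intervention, and those reasons will vary between women because entry spans most of pregnancy and the first days after birth. A factor such as time to delivery or milder illness could emerge as a significant predictor and be reported as a marker of who benefits from family psychoeducation. It might be no more than a marker of who improves anyway. The opposite error is also possible: a factor that helps in one arm and harms in the other can cancel out in a pooled model and be missed.

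**Working it through.** **1. The trial's size, from its own inputs.** The Power Analysis section states that "the sample size has been defined selecting 0.65 as desired level of effect size", with "an α error set at 0.05 and power set at 0.95". Two-sided, by the normal approximation:

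n per arm = 2(1.960 + 1.645)² / 0.65² = 2 × 12.99 / 0.4225 = 61.5, rounded up to 62 (124 in total).

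With the noncentral t distribution, 62 per arm gives power 0.9485 and 63 gives 0.9515. So 63 per arm, 126 in total, reproduces the stated figure. The checks below use 63 per arm. The protocol gives no figure for the predictor analysis.

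**2. What each reading of the model estimates.** Let the log-odds of response be a + b·arm + c·x + d·arm·x, where x is a covariate.

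- Both arms, no interaction term: the coefficient of x is a blend of c and c + d. It is non-zero whenever x is prognostic, even if d = 0.
- Experimental arm only: the coefficient is c + d. It cannot be split into prognosis (c) and the part specific to the intervention (d), because there is no comparison with BTO alone.
- Both arms with the interaction: d is estimated directly. Only d answers the stated question.

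**3. Continuous covariate, purely prognostic (d = 0).** Assumed, not in the protocol: log-odds = −0.6 + 1.0·arm + ln(OR)·x, with x standard normal. At the average covariate value this means response of about 35% in the control arm and 60% in the experimental arm. Share of simulated trials with p < 0.05 for the relevant term:

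| Odds ratio per SD | Pooled, main effect | Experimental arm only | Arm-by-covariate |
|---|---|---|---|
| 1.5 | about 56% | about 30% | about 5% |
| 2 | about 94% | about 68% | about 5% |

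**4. Binary covariate.** Assumed: 50% prevalence; response 30% v 55% or 40% v 65%; 3,000 trials per scenario. Ranges cover the two sets of response rates.

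| Truth | Pooled, main effect | Experimental arm only | Arm-by-covariate |
|---|---|---|---|
| Prognostic only, OR 3 in both arms | 84% | 52–56% | 4–5% |
| Prognostic only, OR 4 in both arms | 96% | 72–75% | 4–5% |
| Effect in experimental arm only, OR 3 | 29–37% | 53–57% | 30–32% |
| Opposite effects, ratio of odds ratios 3 to 4 | about 5% | 17–26% | 30–46% |

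Rows 1 and 3 show the problem most plainly. The experimental-arm-only model behaves almost identically (52–56% against 53–57%) whether the covariate is purely prognostic or purely predictive of benefit. Row 4 shows the pooled model missing a real modifier: its detection rate is no better than the false-positive rate.

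**5. Power of the interaction test at 126 women.** Under the step 4 assumptions there are four cells of 31.5 women. The variance of the log ratio of odds ratios is approximately 2/(31.5·p₀(1−p₀)) + 2/(31.5·p₁(1−p₁)).

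- 30% v 55%: 0.302 + 0.257 = 0.559, SE 0.748.
- 40% v 65%: 0.265 + 0.279 = 0.544, SE 0.737.

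Power for a ratio of odds ratios of 2 is Φ(0.693/0.748 − 1.96) = Φ(−1.03) = 15%, and likewise about 15% with SE 0.737. For a ratio of 3 it is 31–32%, and for 4 it is 46–47%. Power of 80% needs a ratio of exp(2.80 × 0.748) ≈ 8.1, or 7.9 with the smaller SE.

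**The case against.** **The article is condensed.** It lists no terms for the logistic model, and a separate analysis plan may add arm and interactions. A reader might infer that the trial has committed itself to a main-effects model. The text does not say so: it neither includes nor excludes interactions, and its silence on model terms would not be a finding on its own. This limits the point but does not remove it. The article states both a method and an aim, and the method as described does not support that aim under either natural reading.

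**The aim may be more modest.** The sentence introducing the analysis speaks of predictors of response without tying them to one arm, and the later one says only that they are possible predictors. A prognostic model would serve that purpose. This is fair, and it is why rewording is an adequate remedy. But the later sentence does attach response to the experimental intervention, and that is the wording a report would follow.

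**The simulated percentages are not error rates of the plan.** They are the power to detect a genuine prognostic factor. They become mislabelling rates only if the factor is then called a predictor of response to the intervention, and they depend on covariate strengths and response rates that the protocol does not give. This stands; the figures are illustrations over a range.

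**The consequences may be small.** Predictors of treatment response are not among the listed aims, the Discussion says the study can be considered a pilot, and no section says these results will decide who is offered the programme. A reader might infer that selection of women for the programme is at stake; the documents do not go that far.

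**Dichotomising HAM-D.** A reader might count this as a further fault. The efficacy model already uses the continuous score and the responder definition also appears under Primary Outcome, so using it here is a matter of preference.

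**Conclusion.** The point holds as a mismatch between a stated aim and the method described for it. With no treatment term, interaction or analysis set named, the logistic model cannot show that a factor predicts response to the intervention rather than prognosis in general. That conclusion follows from the structure of the model and needs no assumed numbers.

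Its practical size does depend on assumptions. For covariates of moderate to strong prognostic value, the chance of a misleading label runs from roughly one trial in three to nearly all, depending on the covariate's strength and on which arms are analysed. The interaction test keeps it near the nominal 5%.

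The point should be settled before the predictor analysis is run. It concerns a secondary analysis and does not touch the linear model for the 3-month HAM-D score or the sample size. The documents do not support saying that the sponsor has chosen a main-effects model, only that the description given does not support the words attached to it.

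**What to change.** Choose one of two routes and state it in the analysis plan.

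1. **Keep the aim.** Fit the logistic model in all randomised women with arm, covariate and arm-by-covariate terms, for a few covariates named in advance. Call a factor a predictor of response to the intervention only on the strength of the interaction estimate and its 95% confidence interval. Report covariate main effects as prognostic. Label the whole analysis exploratory.
2. **Change the aim.** Keep a model of response, say which arms it uses, and describe the results throughout as prognostic factors for response, with no claim specific to the intervention.

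Neither route needs new data or more women. The first costs a few model terms and brings low power: only very large modifying effects could be shown reliably with 126 women, so a null interaction must not be read as absence of modification. The second costs only wording, but gives up the question of who benefits from the intervention.

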The Edinburgh Postnatal Depression Scale (EPDS) (64) is a simple and short 10-items self-report screening questionnaire initially developed for use in postnatal women to improve detection of postnatal depression. The EPDS allows health professionals to detect women who might need help and require a referral for a full diagnostic assessment. EPDS has satisfactory sensitivity and specificity values and it is also sensitive to changes in severity of depression over time. For the purpose of the present study, the cut-off threshold has been set at ≥ 10 (66). In validation studies, different cut-off points have been found due to clinical, social, cultural and economic diversities (70). The cut-off score for possible depression (i.e., a positive screening result) is ≥13 points but, as suggested by Hewitt et al. (71), a cut-off score ≥ 10 can be used in order to identify patients with both major or minor depression. Moreover, given the observed variability in the performance of the test, the screening procedure could produce both false positives and negatives (72). Therefore, it is essential that this screening tool is complemented by the clinical judgment (73).The Hamilton Depression Rating Scale (HAM-D) (74) is a 17-items questionnaire used to rate the severity of depressive symptoms such as low mood, insomnia, agitation, anxiety and weight loss. The interview and scoring take about 15 min. The score for each item ranges from 0 (not present) to 4 (extreme severity).The Hamilton Anxiety Rating Scale (HAM-A) (75) is a 14-items questionnaire developed to measure the severity of anxiety symptoms, both psychic anxiety (mental agitation and psychological distress) and somatic anxiety (physical complaints related to anxiety). The score for each item ranges from 0 (not present) to 4 (extreme severity).The Global Assessment of Functioning (GAF) (76) is a 100-point rating scale assessing social, occupational, and psychological functioning of adults, with higher scores indicating better level of functioning.The Clinical Global Impression (CGI) (77) scale measures illness severity (CGI-S), global change (CGI-C) and therapeutic response. The CGI-S is rated on a 7-point scale, from 1 (normal) to 7 (the most severely ill patients). The CGI-C scores range from 1 (very much improved) to 7 (very much worse). Treatment response ratings should take into account both the therapeutic efficacy and the treatment-related adverse events, and range from 0 (marked improvement and no side-effects) to 4 (unchanged or worse, and side-effects outweigh the therapeutic effects). Each component of the CGI is rated separately; the instrument does not provide a global score.The Manchester Short Assessment of Quality of Life (MANSA) (78) is a 17-item questionnaire assessing quality of life focusing on satisfaction in twelve aspects of life. For twelve items, the satisfaction is rated on 7-point rating scales, ranging from 1 (“could not be worse”) to 7 (“could not be better”). For five items, the responses are binary (“yes” or “no”). The total MANSA score is the mean of the Likert-item scores.The Family Assessment Device (FAD) (79), based on the McMaster Model of Family Functioning, consists of 7 subscales on family involvement in patient's care (affective involvement, affective responsiveness, behavioral control, communication, problem solving, and roles and general family functioning). Scores range from 1 (“healthy functioning”) to 4 (“unhealthy functioning”).The Family Coping Questionnaire (FCQ) (80) is a self-administered 34-items questionnaire, which has shown a good reliability and external validity. Each item is rated on a 4-level scale, from 1 (“never”) to 4 (“always”). The items are grouped into the following 11 subscales: information on patient's illness; positive communication toward the patient; relatives' maintenance of social interests; patient's involvement in social activities; talking with friends about the patient's condition; coercion; avoidance; resignation; use of alcohol and drugs; collusion; search for spiritual help. The FCQ is widely used for the assessment of coping strategies among relatives of people with severe mental disorders (81, 82).The Pattern of Care Schedule (PCS) (80), a 40-item questionnaire on pharmacological and non-pharmacological treatments as well as on health care access made by the patient. It is compiled by the researcher in collaboration with the patient. If information is inadequate, or if the researcher is not sure about patients' reliability, other sources (e.g., treating physician, relatives, etc.) can be consulted. During the study period, the treating clinician will continue to provide the usual treatment to patient, and–if necessary–to change or adjust the pharmacological regimen. This schedule is used in order to record pharmacological treatments and doses, psychotherapeutic and psychosocial interventions (type of intervention, number of sessions) provided to patients in order to document the BTO.

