### Secondary Outcome

The secondary outcomes include an improvement in the severity of anxiety symptoms (evaluating at the HAM-A), of global functioning and personal functioning (evaluated at the CGI and at the GAF, respectively), an improvement in family members' coping strategies (i.e., an improvement in “problem-oriented” strategies reduction); in the level of quality of life (evaluated at the MANSA) and of family functioning.

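### Choosing the family-coping model by the lowest −2 log-likelihood always returns the largest nested model, so the rule selects nothing

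*Protocol article*

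**What the plan says.** The Data Analysis section of the protocol article describes the coping model in four moves.

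- **Purpose:** to examine "differences in relatives' coping strategies according to patients' clinical features and type of relationship with the patient".
- **Model and estimation:** "a two-level model with fixed independent variables and random intercept, using a maximum likelihood estimation, will be performed". The dependent variable is the mean score on the FCQ subscales, of which the instrument description lists 11.
- **Building candidates:** "adding covariates step by step in order to identify the model with indexes of best fit".
- **Choosing among them:** the criterion is the −2 "loglikelihood value, and the model with the lowest value will be choose".

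Estimates, standard errors, 95% confidence intervals and P-values follow, with significance at p < 0.05. The section gives no penalty for model size, no likelihood-ratio threshold and no requirement that candidate models use the same records. The list of candidate covariates is not given.

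Earlier in the same section there is a separate statement on coping: "Differences in coping strategies and in family accommodation reported by relatives will be evaluated with the same tests". The tests meant are the chi-square and t-tests named just before for comparing the two groups. Under Secondary Outcome, "an improvement in family members' coping strategies" is listed among the secondary outcomes.

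**The concern.** A selection rule has to be able to reject a covariate. This one cannot. Each step gives a model that contains the previous one. A maximum-likelihood fit of the larger model can always reproduce the smaller one by setting the new coefficient to zero, so its maximised likelihood is at least as high and its −2 log-likelihood at least as low. On a fixed set of records, lowest therefore means largest.

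What is at stake is how the coping results will be read. A reader told that the final model was chosen by fit will assume that its covariates earned their place. Under the stated rule they are there because they were tried. The intervals and P-values would come from a model carrying terms that no criterion tested, and its content would depend on where the analyst stopped adding. This applies to each of the 11 FCQ subscales modelled. Table 3 of the article alone lists 10 + 4 + 4 = 18 baseline variables that could be candidates; that count is illustrative only, because the candidate list is not stated.

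A second difficulty is conditional. The −2 log-likelihood is a sum over the records used. If a covariate has missing values and the fit drops those records, models are compared on different data and the values no longer share a scale.

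**Working it through.** **The plan's own figure.** No figure is attached to the selection rule. The one reproducible figure is the total of 126, from "selecting 0.65 as desired level of effect size, an α error set at 0.05 and power set at 0.95". A two-sided two-sample t-test (noncentral t) gives power 0.9485 with 62 per arm and 0.9515 with 63 per arm, so 2 × 63 = 126. That figure is reproduced and not in dispute; 126 is used below only as the number of families.

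**Step 1: algebra.** Let L(k) be the maximised likelihood with the first k covariates. Model k is model k+1 with one coefficient fixed at zero. Hence L(k+1) ≥ L(k), and −2 ln L(k+1) ≤ −2 ln L(k). The minimum over k is at the largest k.

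**Step 2: expected fall from useless covariates.** For a covariate with no effect, the fall is approximately chi-square with 1 degree of freedom, mean 1. For ten such covariates in a single-level normal model with n = 126, the expected fall is n × [ψ((n−1)/2) − ψ((n−11)/2)], with ψ the digamma function: 126 × [ψ(62.5) − ψ(57.5)] = 10.6.

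**Step 3: simulation with ten pure-noise covariates added one at a time.**

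| Set-up | Runs | Lowest −2LL picks all ten | Mean fall in −2LL | AIC picks all ten | 10-df likelihood-ratio test at 0.05 prefers all ten to none |
|---|---|---|---|---|---|
| Single level, n = 126 | 2,000 | 100% | 10.6 | not run | not run |
| Two-level random intercept, 126 families | 500 | 100% | 10.3 | 0.6% | 3.8% |

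The two-level run assumes 2 relatives per family, SD 0.6 and intraclass correlation 0.3. None of these is in the documents. The 100% does not depend on them, because it follows from Step 1.

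AIC works where the stated rule fails because it charges 2 per added parameter against an average gain of about 1. BIC with n = 126 charges ln(126) = 4.84.

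**Step 4: missing covariate values (conditional).** For independent normal data the maximised −2LL per record is about ln(2πσ²) + 1. This is zero at σ = 1/√(2πe) = 0.24. Above that SD, each dropped record lowers the total; below it, each raises the total. The FCQ item scale is given ("Each item is rated on a 4-level scale, from 1 (“never”) to 4 (“always"), but no subscale SD is. At assumed SDs of 0.5, 0.6 and 0.75 the value per record is 1.45, 1.82 and 2.26.

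Next, compare a complete covariate with a true slope of 0.4 residual SD against a pure-noise covariate missing in 10% of records, single level, n = 126. The true covariate lowers the residual variance by the factor 1.16, and the noise model keeps about 113.4 records. With c the per-record value, the noise model's expected advantage is about 126c − 113.4 × (c + ln 1.16):

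| Assumed residual SD | c | Approximate advantage of the noise model | Simulated share of runs in which it has the lower −2LL |
|---|---|---|---|
| 0.6 | 1.82 | +6.1 | about 70% |
| 0.5 | 1.45 | +1.5 | about 55% |
| 0.4 | 1.01 | −4.2 | about one third |
| 0.3 | 0.43 | −11.4 | about 12% |

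The direction changes within a plausible range of SDs. It also depends on the true effect and the clustering. In the two-level set-up above, with a weaker true effect (0.2 SD per SD), the noise covariate won in 96%, 100% and 100% of runs with 5%, 10% and 20% of families missing.

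**The case against.** The best defence is that the authors meant something more standard. The building step speaks of indexes of fit in the plural, and P-values are to be calculated, so likelihood-ratio tests or information criteria may have been intended. This is possible, but the sentence that fixes the final choice names only the −2 log-likelihood and says that the lowest value wins. It is a stated decision rule, not a detail left to a fuller plan. The rule can also rank models of equal size on the same records, which is a legitimate use, but any model that adds to them still wins.

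It is also fair that the reach is small. The model is descriptive and does not touch the HAM-D analysis, the sample size or the two-group coping tests. That stands.

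Two stronger readings are tempting, and the documents support neither.

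- A reader might infer that the rule in general rewards covariates with missing values. That requires fits that drop incomplete records, and its direction depends on the outcome's SD and the size of the true effects. The article gives no missing-data rule and no FCQ SD. What can be said is that −2 log-likelihood values would not be comparable between models, and that incomplete covariates may be favoured.
- A reader might infer that the model wrongly leaves out treatment arm, so that the secondary coping outcome is not compared between arms. Arm is not named, but the model's stated purpose is association with clinical features and type of relationship, and its covariate list is open. Between-group differences in coping appear to be assigned to the chi-square or t-tests. Building arm, visit and baseline score into this model would be a redesign, not the correction of an error.

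**Conclusion.** The rule is wrong as written. On a common set of records it returns the largest nested model every time. That is an algebraic result, confirmed in 100% of simulated runs, and it needs no assumption beyond the article's own statements of maximum likelihood, stepwise addition and lowest value. Useless covariates lower the criterion by about 1 each on average, so the final model would be overfitted to the extent that the candidate list contains covariates without effect. The list is not stated, so the extent cannot be given.

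The loss of comparability through missing covariate values is a conditional aggravation. It rests on case-wise deletion, and whether incomplete covariates would gain depends on an SD that the article does not give.

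The defect is confined to a secondary or exploratory analysis of relatives' coping. It should be corrected, but it does not bear on the trial's main conclusion.

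**What to change.** Replace the selection sentence in Data Analysis. Two forms would do:

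- choose the model with the lowest AIC or BIC, naming which; or
- compare nested models by likelihood-ratio test at a stated level.

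In either case, state that all candidate models are fitted by maximum likelihood to one common set of records, for example those complete on every candidate covariate.

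The cost is a change of wording. AIC and BIC are computed from the same −2 log-likelihood and the number of parameters (BIC also uses the sample size). No new data, visits or software are needed, and the sample size does not change.
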